### 8.2.4 General statistical considerations

The data will primarily be presented with summary statistics. Summary statistics will include at least number of subjects, mean, standard deviation, median, minimum and maximum for continuous data, and frequency and percentage for categorical data. All data collected will be listed by subject and treatment group.

### 8.2.5 Demographic and baseline characteristics

The demographic and baseline characteristics of the subjects will be presented using descriptive summary statistics.

### 8.2.6 Analysis of efficacy variables

For the primary variable of the study, the proportion of hospitalizations will be estimated within each treatment group. The main analysis will be made using a logistic regression model. The methods of analysis of all efficacy variables will be

provided in the SAP. At least, analysis of all primary and secondary efficacy variables will be performed for both the PP and ITT datasets.

## 8.2.7 Analysis of safety variables

### 8.2.7.1 Evaluation of adverse events

AEs will be collected starting from the moment of the ICF signature, but AEs occurring before and after IMP administration will be reported separately. All AEs reported during the study will be classified by system organ class and preferred terms using the Medical Dictionary for Regulatory Activities (MedDRA) coding system, and according to severity of the AE (mild, moderate, severe) and causality to the IMP. The number and proportion (%) of subjects having each AE and the number of events will be tabulated overall and by treatment group.

### 8.2.7.2 Clinical safety evaluations

The clinical safety data will primarily be analyzed using summary statistics. Physical examination findings will be evaluated with descriptive statistics. The actual values of systolic and diastolic blood pressure, heart rate, body temperature, SaO2 and respiratory rate will be presented using summary statistics. 12-lead ECG results will be summarized and tabulated as normal, abnormal, not clinically significant and abnormal, clinically significant.

### 8.2.7.3 Clinical safety laboratory evaluations

Laboratory safety variables and their changes from baseline will be summarized using descriptive statistics and categorized as normal, abnormal, not clinically significant and abnormal, clinically significant. The values will also be categorized into low, normal and high according to their reference ranges. Clinically significant laboratory abnormalities will be reported in the study report.

## 8.2.8 Analysis of pharmacokinetic, pharmacogenetic and immunogenetic variables

The pharmacokinetic, pharmacogenetic and immunogenetic study results will not be entered into the eCRF, and these results will be analyzed and reported separately by the participating analysis service providers and collaborating laboratories. These reports will be included as appendices into the main clinical study report.

The pharmacokinetic analysis is performed to confirm drug exposure and to assess Cmax and rate of drug elimination. No thorough pharmacokinetic inferences will be aimed at.

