#### **Duration of treatment**

IMPs will be taken twice daily by mouth, with meals, for seven consecutive days. Because of the slow elimination of HCQ, the treatment period of this study is defined as starting from the first IMP intake and ending at the 28-day follow-up visit.

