## 6.2 Treatment period

The treatment period will last 4 weeks and the actual treatment 7 days. During the treatment period, the subjects will receive HCQ or placebo capsules twice daily with meals during 7 days. In addition, all subjects will receive standard care for their Covid-19 infection, according to local treatment practice. This includes daily telephone contacts with patients who have symptoms. The script of the daily telephone interviews includes questions on possible suicidal ideation and impairment of mental health. Should the answers to these questions reveal significant adverse changes from baseline or an elevated risk for self-harm, the investigator will be informed, and will then take the necessary actions to provide appropriate psychiatric evaluation and care for the subject, without delay. The subjects will be provided with finger-tip pulse oximetry devices and with instructions on their use during the first 14 days of the treatment period.

On Day 8, all subjects will be contacted by telephone for an interview on symptoms, concomitant medications and possible AEs.

Approximately 2 weeks and 4 weeks after start of drug intake, the subjects will visit their study site for assessments. Safety laboratory tests will be taken at these visits, as well as nasopharyngeal swab samples for SARS-CoV-2 PCR analysis and blood samples for analysis of SARS-CoV-2 antibody titres, other Covid-19-related biomarkers and HCQ concentration analysis. The GAD-7 questionnaire will be completed by the subjects. In addition, they will be asked about symptoms, concomitant medications and possible AEs that might have occurred since the last contact. At the 2-week visit, body temperature and SpO2 will also be measured, and the participant diaries will be collected.

Because of the slow elimination of HCQ, the treatment period of this study is defined as starting from the first IMP intake and ending at the 4-week visit.

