#### 7.4 Assessments of pharmacokinetics, pharmacogenetics and immunogenetics

Blood samples will be collected at the 2- and 4-week visits in order to monitor treatment compliance by concentration analysis of HCQ. The HCQ concentration results will additionally be used to perform population pharmacokinetic modeling in order to evaluate associations between drug exposure and relevant patient outcomes.

A separate whole-blood sample (with EDTA as anticoagulant) will be collected from consenting participants for later DNA extraction and pharmacogenetic (PG) analysis of genetic variation in drug metabolizing enzymes and exploration of immunogenetic associations in the study outcomes. The PG samples will be tested with the Abomics PGx test platform that includes the genes for ALDH2, BCHE, CYP1A2, CYP2B6, CYP2C19, CYP2C9, CYP2D6, CYP3A5, DPYD, F2, F5, G6PD, IFNL3, SLCO1B1, TPMT, UGT1A1 and VKORC1, of which at least CYP2D6 is known to be involved in the metabolism of HCQ. The PG results will be used for interpretation of the HCQ-related outcomes of the study. Immunogenetic analysis is carried out for HLA haplotypes, but it may be expanded to other genes related to immune functions and susceptibility to Covid-19 infection and its manifestations. The blood sample for DNA extraction may be collected at any time during the study. The PG analysis and the immunogenetic analysis are exploratory and optional, and will only be carried out if sufficient numbers of samples become available for meaningful analysis.

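### Section 8.2.8 names Cmax as a pharmacokinetic aim, but the only post-dose samples fall about 7 and 21 days after the last dose, so no peak can be assessed

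*Protocol*

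**What the plan says.** **Aim.** Section 8.2.8 gives the purpose of the pharmacokinetic work: "The pharmacokinetic analysis is performed to confirm drug exposure and to assess" Cmax and the rate of elimination. It then limits the ambition: "No thorough pharmacokinetic inferences will be aimed at". Section 7.4 adds a further use of the same results, to "perform population pharmacokinetic modeling in order to evaluate associations between drug exposure and relevant patient outcomes". The abbreviation list defines Cmax as the maximum concentration observed.

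**Dosing.** The synopsis, under Duration of treatment, says: "IMPs will be taken twice daily by mouth, with meals, for seven consecutive days".

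**Sampling.** Section 7.4 says: "Blood samples will be collected at the 2- and 4-week visits in order to monitor treatment compliance by concentration analysis of HCQ". Section 6.2 fixes the time origin: "Approximately 2 weeks and 4 weeks after start of drug intake, the subjects will visit their study site for assessments". Sections 5.5 and 7.3.2 name the same two visits. Footnote 3 of Table 1 attaches HCQ sampling to a row that is also marked at screening, but a screening sample would be taken before any dose.

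**Hospitalized subjects.** Section 3.2 says that a subject's participation ends on hospitalization. Section 4.7 lists the need for hospital treatment as a reason to stop dosing, and Section 13 does the same for hospitalization for any reason. Both then encourage subjects who stop study drug to attend all visits and complete all assessments.

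**The concern.** The protocol fixes both the aim and the sampling times, and the two do not fit. No blood is scheduled during dosing or in the week after it. By the protocol's own definition, Cmax would be the larger of two values taken well into elimination, usually the week-2 one. It would then appear as a peak in a report appended to the clinical study report.

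The exposure-outcome work in Section 7.4 has a related weakness. A subject admitted before week 2 has either no concentration (if Section 3.2 is followed) or one that may reflect treatment stopped by the admission (if Sections 4.7 and 13 are followed). In the first case early events drop out. In the second, the outcome can lower the exposure that is meant to explain it.

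**Working it through.** **1. Timing.** The last dosing day is Day 7, and the visits are at about Day 14 and Day 28 from start of intake.

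- First sample: 14 − 7 = 7 days after the last dose.
- Second sample: 28 − 7 = 21 days after the last dose.
- Samples scheduled during dosing: none.

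**2. Can these two samples inform a peak?** Take a two-phase decline after the last dose, C(t) = A·exp(−at) + B·exp(−bt), with B = 1. The concentration at the last dose is A + B, and A is varied from 0 to 3 so that this peak rises from 1 to 4. The protocol gives no half-lives, so I assumed 0.25 to 1 day for the initial phase and 5 to 40 days for the terminal phase. The case most favourable to detecting a peak is 1 day and 5 days:

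- t = 7: the extra term is 3 × 2^(−7) = 0.0234, against 2^(−7/5) = 0.379, a change of 6.2%.
- t = 21: the extra term is 3 × 2^(−21) = 0.0000014, against 2^(−21/5) = 0.0544, a change of 0.003%.

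Over the whole assumed grid, a fourfold rise in the peak moves the first sample by 0% to about 6% and the second by less than 0.01%. The data would carry almost no information on the peak.

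**3. What the samples do support.** A quantifiable level at week 2 confirms that drug was taken. The two values give one slope per subject, ln(C14/C28)/14 per day, with no spare point to check that the decline is log-linear. Hence exposure and a crude terminal decline.

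**4. Early admissions and dose taken.** If admission stops dosing, exposure depends on when it happens. A subject admitted at the start of Day 4 would have taken 600 + 400 + 400 = 1400 mg of the planned 3000 mg.

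**5. Events available for an exposure-outcome analysis.** The plan's own figure comes first. Section 8.1 assumes 15% against 7.5%, with 80% power; the synopsis gives a two-sided 5% level. With pooled variance under the null and mean proportion 0.1125:

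n = [1.960·√(2 × 0.1125 × 0.8875) + 0.842·√(0.15 × 0.85 + 0.075 × 0.925)]² / 0.075² = (0.876 + 0.373)² / 0.005625 ≈ 277.5, which rounds up to 278 per group, as stated.

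Expected HCQ-arm admissions are 278 × 0.075 = 20.85, about 21. The protocol does not say when admissions occur, so the share before the 2-week visit is an assumption:

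| Assumed share before week 2 | Before the sample | Left after it |
|---|---|---|
| 25% | 5.2 | 15.6 |
| 50% | 10.4 | 10.4 |
| 75% | 15.6 | 5.2 |
| 90% | 18.8 | 2.1 |

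The 20.85 itself assumes the full 50% reduction. With no effect it would be 278 × 0.15 = 41.7, and each row would double.

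**The case against.** The best defence is that the pharmacokinetic work is exploratory, is reported separately, and already disclaims thorough inference. Sparse sampling suits two of the three stated aims, and a population model can output a peak from sparse data. Most of that stands. It does not rescue Cmax, which the sentence just before the disclaimer names as an aim. A model-based peak would come from the model's assumptions rather than from these samples.

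A reader might also infer several stronger points that the document does not support:

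- **That subjects admitted before week 2 certainly have no sample.** Section 3.2 points that way, but Sections 4.7 and 13 point the other way.
- **That the exposure-outcome analysis targets the four-week primary endpoint.** Section 7.4 speaks only of relevant outcomes. Week-4 PCR or antibody results, or later events, would fit equally well.
- **That the result would suffer from immortal-time bias.** All sampled subjects share the same event-free period before the sample, so it is not credited to one exposure level over another. The fair description is selection and loss of early events.
- **That Sections 7.4 and 8.2.8 contradict each other.** Exploratory modelling of sparse data is compatible with modest inference. They need the same stated scope, not a choice between them.
- **That the primary result is weakened through the compliance check.** Section 8.2.3 defines the intention-to-treat and per-protocol sets without reference to concentrations.

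**Conclusion.** The point holds for Cmax. The protocol names an aim that its sampling scheme cannot meet, and the value reported under that name would be a washout concentration taken about a week after dosing ended. This rests only on the stated dosing days and visit times; the assumed half-lives serve only to show how little a model could recover.

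The point on clinical events is conditional. Any analysis that relates concentrations to admissions before the 2-week sample is affected by missing samples or by shortened dosing, depending on which of the conflicting sections is followed. The number of events lost cannot be derived from the protocol. The range of about 16 down to 2 remaining out of 21 depends on the assumed 25% to 90% early share and on the planning effect.

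The matter is minor: it concerns exploratory work only, and the primary analysis and the sample size are unaffected.

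**What to change.** - **Section 8.2.8:** delete Cmax. State the aim as confirming exposure and describing the decline between the 2-week and 4-week samples.
- **Section 7.4:** align the population modelling with that scope. Where concentrations are related to clinical events, use a landmark at the 2-week sample: include subjects who are sampled and free of the event at that point, and count only later events. Admissions between the 2-week sample and week 4 can still be used, so no general bar on the four-week endpoint is needed.
- **Sections 3.2, 4.7 and 13:** reconcile what follow-up and sampling apply after a hospitalization. This review takes no position on which rule is right.

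The cost is a change of wording, with no added samples or visits. The downside is a narrower exploratory exposure-outcome claim that rests on fewer events.

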## 8.3 Data management

Detailed information on data management (DM) will be given in a separate Data Management Plan specifically written for this study.

### 8.3.1 Database design

The study database and data entry screen design, as well as edit checks will be defined according to the corresponding eCRF and the study protocol.

### 8.3.2 Data entry

Data will be collected on source data forms and entered into an eCRF designed in accordance with the study protocol. The investigator or designated study site personnel will enter subject data into the eCRF as soon as possible during or after the subject's visit. All data entries in the eCRF should be consistent with the source documents. The investigator will electronically sign the data to confirm that the information is accurate and correct.

### 8.3.3 The query process

The Study Monitor will review the eCRFs and compare them with the relevant source documents to ensure the validity and accuracy of the study data. If corrections are needed, the Study Monitor will raise a query in the eCRF. The investigator or designated member of the study site personnel will answer any queries and make the needed corrections or alterations.

### 8.3.4 Medical encoding

AEs and medical history verbatim terms will be coded using MedDRA (version 23.1).

### 8.3.5 Database lock

When all data have been entered and discrepancies solved, the study database can be locked. The locked database is used in the final statistical analyses and in the reporting of the study results.

## 8.4 Software

Viedoc™ (Viedoc Technologies AB, Uppsala, Sweden) will be used as an electronic data capture (EDC) system for this study.

## 9 QUALITY CONTROL AND QUALITY ASSURANCE

During the clinical execution of the trial, the principles of GCP are followed throughout the study. For data management and statistics, the standard operating procedures of 4Pharma are followed.

The analyses of safety laboratory assessments will be performed at the laboratory of SataDiag. The analysis of HCQ concentrations in whole blood samples is planned to be performed at the Bioanalytical Laboratory of the University of Turku, Institute of Biomedicine. Diagnostic PCR testing will be carried out at SataDiag and antibody testing from serum will be performed by collaborating researchers at TYKSLAB and the University of Turku. Optional pharmacogenetic testing for drug metabolizing enzymes will be carried out by Abomics Ltd. HLA haplotyping will be performed by TYKSLAB, the accredited hospital laboratory of Turku University Hospital. Laboratory quality certificates will be available.

The study will be monitored by Turku Clinical Research Centre (TurkuCRC). The monitor is allowed to monitor the study as frequently as necessary to ensure that the data recording and protocol adherence are satisfactory. The eCRFs and related source data will be reviewed in sufficient detail.

A curriculum vitae in English will be obtained from all investigators who sign the protocol and from other relevant persons.

## 10 ETHICAL CONSIDERATIONS

This study will follow the relevant regulations and guidance for biomedical research involving human subjects, such as the Declaration of Helsinki, GCP, and national and EU legislation. Special emphasis will be put on the well-being of the subjects.

Prior to initiation of the study, the study protocol, the subject information leaflet and the ICF and the texts of any advertisements used for the recruitment of study subjects will be submitted to and approved by an independent Ethics Committee (EC). Additionally, the EC will be notified of any other possible materials to be given to the subjects (e.g. study subject diary, participant card). The study will be authorized by the CA (the Finnish Medicines Agency, Fimea) before its commencement.

The study subject candidates will be provided with both verbal and written information on the study, its risks and benefits. They are encouraged to ask questions on the study. After having had enough time to consider their participation they may sign the ICF. No study procedure will be implemented prior to obtaining written IC that is signed by the subject at the time of consent. A copy of the signed ICF will be given to the subject. The investigator will keep each subject's signed ICF on file for inspection by a regulatory authority at any time.

The subjects are told what information will be collected of them and how. The collection of personal information is described in compliance with the EU General Data Protection Regulation; the description is kept in the ISF and is made available to the subjects, if they wish. The investigator assures that the privacy of the subjects, including their personal identity and all other medical information, will be maintained at all times.

The subjects are urged to report all AEs to the study personnel and they are given phone numbers of the investigator and study nurses whom they are instructed to call if they observe AEs, or in other urgent study-related issues.

A Steering Committee (SC) will provide oversight of the study. One of the tasks of the SC will be to provide recommendations to the Sponsor and the Coordinating Investigator on whether enrolment of participants into the study should be continued or terminated, or whether modifications should be introduced into the study protocol in the form of a substantial amendment. No formal interim analysis of the accumulating study results has been planned, but the SC and the data management (DM) provider of the trial will perform unblinded follow-up of all hospitalizations and all deaths occurring in the study population, in order to be able to call for termination or modification of the trial.

Substantial changes to the final approved study protocol will only be initiated with the EC's favourable opinion of a written amendment, except when necessary to eliminate immediate hazards to the subjects. When the change involves only logistics or administration, it is considered non-substantial, and needs not be submitted to the EC or the CA. The CA will also be notified before adopting a substantial amendment.

After the study has been completed or terminated, and the study report prepared, the EC and CA will be notified of the study results.

The study procedures are minimally invasive, but study participation involves certain risks for the subjects. The volume of blood to be collected for the purposes of the study is less than 100 ml. Half of the participants will be exposed to treatment with HCQ, a drug known to have adverse effects in some individuals. HCQ-related risks will be minimized by careful subject selection and close follow-up of the participants. The subjects may also derive benefit from their participation if HCQ has efficacy in the treatment of Covid-19 infection. For study site personnel, execution of the study procedures adds to their contacts with patients with Covid-19 infection, and may increase their risk of contracting the disease. Appropriate precautions will be taken at all study sites to minimize this risk.

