### **Number of Subjects**

Approximately 600 subjects are planned to be included in the study by the summer of the year 2021, but actual enrolment numbers will depend on the development of the Covid-19 epidemic in Satakunta and in other participating regions of Finland. Enrolment will be discontinued prematurely if new information becomes available that mandates study discontinuation, e.g. for futility or for proof of efficacy of HCQ or another type of treatment of Covid-19 infection in the patient population targeted by this study. Also, enrolment may have to be terminated at any participating study site if sufficient resources can no longer be allocated to ensure adequate study conduct and participant safety. A Steering Committee (SC) will provide oversight of the study. One of the tasks of the SC will be to provide recommendations to the Sponsor and the Coordinating Investigator on whether enrolment of participants into the study should be continued or terminated, or whether modifications should be introduced into the study protocol in the form of a substantial

amendment. The SC and the data management (DM) provider of the trial will perform unblinded follow-up of all hospitalizations and deaths occurring in the study population in order to be able to call for termination or modification of the trial. No other interim analysis of the accumulating study results has been planned.

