#### Sample size considerations:

The number of hospitalizations due to Covid-19 infection within four weeks of entry into the study is a main outcome measure of the current study. Assuming a hospitalization rate of 15 % in the study population, and a 50 % reduction in the risk for hospitalization in the group treated with HCQ, a treatment group size of 278 provides 80 % power to detect a statistically significant treatment effect at a two-sided  $p < 0.05$ . As the actual risk of hospitalization in the study population is unknown, and also because a treatment effect

size of less than 50 % is considered potentially clinically significant, both expansion of the trial beyond the initial catchment region of Satakunta and meta-analysis by combining the study results with those derived from other similar patient populations are planned.

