### 8 STATISTICS AND DATA MANAGEMENT

#### 8.1 Estimation of sample size

Up to 600 subjects will be included in the study. The number of hospitalizations due to Covid-19 infection within four weeks of entry into the study is a main outcome measure of the current study. Assuming a hospitalization rate of 15 % in the study population, and a 50 % reduction in the risk for hospitalization in the group treated with HCQ, a treatment group size of 278 provides 80 % power to detect a statistically significant treatment effect at  $p < 0.05$ . Since the other efficacy-related evaluations are of secondary/explorative nature in this study, no formal sample size calculations have been performed for these endpoints. For a hospitalization risk of 10 %, the group size required for 80 % power would be 435, and for a risk of only 5 %, 906 subjects per group would be required for 80 % power. As the true risk of hospitalization in the study population is unknown, and as an effect size of less than 50 % may also be considered clinically significant, both expansion of the trial beyond the initial catchment region of Satakunta and meta-analysis by combining the study results with those derived from other similar patient populations is intended.

Detailed information on the power calculations will be provided in a separate Statistical Analysis Plan (SAP). The power calculations were made using nQuery Advanced version 8.5.

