### 13 CRITERIA FOR PREMATURE STUDY TERMINATION

The study may be discontinued at the discretion of the Principal Investigator or the Sponsor based e.g. on the occurrence of the following:

- ADRs unknown to date in respect to their nature, severity, and duration or the unexpected incidence of known ADRs;
- New information becomes available that mandates study discontinuation, e.g. for futility or for proof of efficacy of HCQ or another type of treatment of Covid-19 infection in the patient population of this study.
- Other medical or ethical reasons affecting the continued performance of the study.
- Difficulties in the recruitment of subjects.
- Significant deviations from the study protocol.

The investigator will inform the EC and the Sponsor will inform the CA if the study is terminated prematurely. The Sponsor reserves the right to prematurely terminate the study for valid scientific or administrative reasons. The investigator will proceed to appropriate actions concerning the study subjects in the case of premature termination of the study.

A study site may withdraw from further subject recruitment at any time if sufficient resources can no longer be allocated to proper execution of the study procedures. Already enrolled subjects should be treated and followed up according to the study protocol even if a site is withdrawn from further enrollment activities.

Individual study subjects are free to withdraw from further study treatment and from further study procedures if they wish. In addition, subjects should be withdrawn by the investigator from further study medication in case the patient must be hospitalized for any reason, if the subject starts a prohibited medication or if an AE severe enough to justify discontinuation of treatment with HCQ develops. The investigator may withdraw a subject from the study at any time based on the investigator's clinical judgement. A subject will also be withdrawn from further IMP administration if she/he fails to comply with the trial protocol, or if the discontinuation is otherwise in the best interest of the subject.

Subjects who discontinue the study medication prematurely will be encouraged to attend all study visits and complete all study assessments.

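### The committee's running unblinded review covers the primary endpoint and is nowhere barred from acting on apparent benefit, while the sample size spends the full 5% on one final test

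*Protocol*

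**What the plan says.** - **Endpoint.** Section 2.4 makes Covid-19 hospitalizations within four weeks of entry the primary endpoint.
- **Who sees what.** Under Section 10 the Steering Committee and the data management provider "will perform unblinded follow-up of all hospitalizations and all deaths occurring in the study population, in order to be able to call for termination"; modification is a second aim. The synopsis (Number of Subjects) says the same. In both places the committee also advises on whether enrolment continues and on substantial amendments.
- **Purpose.** Section 3.2 has the treatment code opened when a subject dies or is hospitalized. De-identified unblinded information on these events goes to the committee, for the stated purpose of evaluating participant safety.
- **Interim analysis.** Section 10 says that no formal one is planned. The synopsis says "No other interim analysis of the accumulating study results has been planned".
- **Stopping grounds.** Section 13 lists, among reasons for the Principal Investigator or Sponsor to discontinue, "New information becomes available that mandates study discontinuation, e.g. for futility or for proof of efficacy of HCQ or another type of treatment". The synopsis has a parallel sentence on enrolment. Neither gives a threshold.
- **Error rate.** The synopsis states that "a treatment group size of 278 provides 80 % power to detect a statistically significant treatment effect at a two-sided" 0.05. Section 8.1 repeats the size and the 0.05 without naming the side.
- **Timing.** Section 8.2.1 promises the SAP before database lock, which can be after all of these reviews.

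**The concern.** Allocation is close to 1:1 (Section 10 says half the participants receive HCQ), so a running count of hospitalizations by arm is in effect a running look at the primary comparison. The body that sees it is there to call for termination or modification. The protocol does not say that such a call may rest only on harm, and it sets no rule for a call that rests on benefit.

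Repeated looks matter for the final claim only if they can change the trial in favour of that claim. A committee free to recommend stopping because HCQ looks effective gets several chances to see a chance difference, and the plan reserves no error rate for them. A trial stopped on apparent benefit would also tend to overstate the effect, and its p-value would not be valid at the nominal level. This is the trial's one formal hypothesis test, because Section 8.2.2 treats the other endpoints mainly descriptively.

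**Working it through.** **1. Is any error rate set aside for looks?**

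Inputs from Section 8.1 and the synopsis: control rate 15%, a 50% relative reduction (so 7.5% on HCQ), two-sided 0.05, 80% power. With the pooled-variance formula and no continuity correction,

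n = [1.960·√(2·p̄·(1−p̄)) + 0.842·√(p₁(1−p₁) + p₂(1−p₂))]² / (p₁−p₂)², with p̄ = 0.1125.

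- First term: 1.960 × √(2 × 0.1125 × 0.8875) = 1.960 × 0.4469 = 0.876
- Second term: 0.842 × √(0.1275 + 0.0694) = 0.842 × 0.4437 = 0.373
- n = (0.876 + 0.373)² / 0.075² = 1.561 / 0.005625 ≈ 277.5, rounded up to **278**

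The same formula gives 435 and 906 for control rates of 10% and 5%, matching Section 8.1. A one-sided test would give 219 and a continuity-corrected one 304, so neither was used. The plan's figures therefore correspond to one fixed analysis that uses the whole two-sided 5%.

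**2. What would unadjusted looks cost?**

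The protocol gives no number or timing of looks, so these schedules are assumptions. For K equally spaced looks with no true effect, Zₖ is the sum of k independent standard normal increments divided by √k. Two rules were simulated (1,000,000 paths), each with a two-sided final test at 1.96:

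| Looks, including the final | Early stop for benefit only | Early stop in either direction |
|---|---|---|
| 2 | 6.7% | 8.3% |
| 3 | 7.8% | 10.7% |
| 5 | 9.6% | 14.2% |
| 10 | 12.1% | 19.3% |

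The benefit-only column is the relevant one, because stopping when HCQ looks harmful is not a false claim of efficacy. Taking off about 2.5% for final results in the harm direction, the chance of a false benefit claim is about 4.2% with 2 looks (6.7 − 2.5) and 7.1% with 5 (9.6 − 2.5), against a nominal 2.5%.

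**3. The same for looks driven by events.**

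Setting: 600 subjects, 1:1, no true effect, pooled two-proportion z-test, looks from the 10th hospitalization. The event rates are 15%, 11.25% (the planned average of 15% and 7.5%) and 5%. At these rates 600 subjects give about 90, 68 and 30 events.

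| Schedule | Benefit-only early stop, at 15% / 11.25% / 5% |
|---|---|
| Every 10 events | about 13% / 11% / 7% |
| Every event | about 16–18% / 15–16% / 11% |

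The ranges reflect runs with different block sizes and 4,000 or 20,000 trials per scenario.

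**4. Does a strict boundary cure it?**

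With an interim threshold of two-sided p < 0.001 and a final test at 0.05, the overall error stays at about 4–5.5% in every schedule in step 3.

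**5. Do the passages agree?**

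| Place | What it implies |
|---|---|
| Section 3.2 | Unblinded data go to the committee for safety |
| Section 10 | Follow-up supports termination or modification in general; no formal interim analysis |
| Synopsis, Number of Subjects | Same follow-up, implicitly counted as an interim analysis |
| Section 13 | Efficacy and futility are grounds to stop; source of the evidence not stated |

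None of the four excludes a recommendation based on apparent benefit in the trial's own data.

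**The case against.** The strongest reply is that this is safety oversight. Section 3.2 says so, and the sentence in Section 10 sits among the ethical considerations and not in the statistics. A review that can stop only for harm or futility does not raise the false-positive rate for benefit. That principle stands, and safety is a natural reading. But the synopsis and Section 10 describe the power to act as termination or modification in general, and no sentence narrows it.

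Three stronger readings are tempting, and the document does not support them:

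- **Section 13 authorises efficacy stopping on the trial's own data.** A reader might infer this. But the clause speaks of new information and covers other treatments too. In a two-arm placebo trial, evidence on another treatment must come from outside, so external evidence is the more natural meaning. The decision there also belongs to the Principal Investigator or Sponsor. Internal data are not expressly excluded, so one clarifying word is worth adding.
- **The expansion in Section 8.1 will be steered by results by arm.** The expansion is geographic, under a ceiling of 600, and motivated by an unknown event rate and a possibly smaller effect. Nothing ties it to arm-level data.
- **The true error rate is near 30%.** Figures of 17–30% arise only if someone tests after every event at nominal 0.05 and harm-direction crossings are counted. The protocol describes no such testing.

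Nor does every early stop exaggerate the effect. Stops for harm, futility, poor recruitment or outside evidence do not overstate benefit.

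It may also be said that an SAP or committee charter could hold the rule. It might, but the protocol itself grants the access and denies a formal interim analysis, and the SAP may come after the looks.

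**Conclusion.** The point holds in a limited form. The protocol gives running unblinded sight of the primary endpoint to bodies that can call for termination or modification. It does not exclude acting on apparent benefit, describes the follow-up inconsistently, and plans its test as a single fixed analysis.

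The size is conditional. If looks were acted on for benefit at an unadjusted 0.05, the overall two-sided error would be about 7% (2 looks), 10% (5 looks), 7–13% (every 10 events) or 11–18% (every event). These figures rest on assumed schedules and on early stopping for benefit only. They show what the open wording allows and do not predict what the committee would do. If the review can stop the trial only for harm or futility, there is no inflation. The effect of a data-driven modification was not computed, because the protocol does not say what form it could take.

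**What to change.** Align the synopsis (Number of Subjects) and Sections 3.2, 10 and 13, so that they say the same thing:

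1. The committee's unblinded review is for participant safety and may not lead to stopping or modification for apparent efficacy. If efficacy stopping is wanted, declare it as an interim analysis with a strict boundary, for example Haybittle–Peto at two-sided p < 0.001, which leaves the final test at about 0.05.
2. Any futility look is non-binding.
3. Any change of sample size is decided from the pooled, blinded hospitalization rate only. Under the planning assumptions that rate is (15% + 7.5%) / 2 = 11.25%.
4. New information on efficacy, in the synopsis and Section 13, means evidence from outside the trial.
5. Use one description of the follow-up, so that the synopsis and Section 10 agree on whether it counts as an interim analysis.

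The cost is protocol and charter wording, with no extra subjects. The downside is that the committee gives up discretion to stop early for a modest apparent benefit.
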